### Statistical analysis

All statistical analyses in the study will be carried out by an analyst who is blinded as to the allocated intervention. The primary efficacy will be compared by an intention-to-treat analysis including all randomized patients.

Regarding the primary outcome (the 12-month survival rate), the Cox regression model method will be used to calculate the hazards ratio and the 95% confidence interval (CI). The non-inferiority of the new surgical method and the conventional method is determined according to whether the upper limit of the 95% CI of the HR is less than 1.3. If the upper limit of the 95% CI is less than 1.3, the non-inferiority is accepted. Otherwise, a non-inferiority conclusion cannot be reached.

For the secondary outcomes, the OS curves will be estimated using the Kaplan–Meier method. Continuous variables will be assessed for normality and equality of variances between groups. Discrete variables will be summarized by frequencies/proportions. For continuous variables, analysis of variance and/or regression will be used, where appropriate (hospital length of stay, hospitalization expenses). The comparison of the two groups with respect to frequencies/proportions will be performed using the *χ*^2^ test and, if necessary, Fisher’s test (proportion of patients who need ventricular-peritoneal shunt after surgery, incidence of postoperative hydrocephalus, postoperative intracranial infection rate). The ranked data of the two groups will be compared using the Wilcoxon rank-sum test (mRS).

At the annual monitoring meeting of the Data and Safety Monitoring Board, the treatment effectiveness (the 12-month survival rate) will be compared between the two groups. If one group has significantly more hazards than the other one (upper limit of the 95% CI of the hazards ratio is more than 1.3), the trial will be terminated.

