### Sample size

The sample size calculation results in a requirement of 956 patients. For EVD, the mortality rate is 23% in a meta-analysis of 4 randomized and 8 observational studies of patients with IVH [11]. In the CLEAR III trial, the mortality rate of the IVH patients treated with EVD plus rtPA is 18% at 180 days [13]. And the reported mortality rate of IVH patients treated with endoscopic surgery at 1 year ranges from 10 to 30% [1, 19, 20]. Based on previous studies and our own experience, we assume a 1-year overall survival rate of 70% (mortality rate of 30%) in both the reference group and the new surgical group. We plan for the trial to show non-inferiority of a new surgical method to the conventional method with a hazard ratio (HR) margin of 1.3 [21, 22]. The principle of the sample size calculation of a non-inferiority trial is different from that of a superiority trial where you want to demonstrate that one treatment or intervention is better than another. In the context of non-inferiority trials, the non-inferiority limit is used to calculate the sample size. The percentage for those on the experimental treatment is no worse than the percentage for those on the control treatment by the non-inferiority limit. In our study, the non-inferiority limit of the hazards ratio (HR) is set to 1.3. Accounting for a potential dropout rate of 5%, 956 patients (478 in each group) are needed to be enrolled, which ensured a power of 80%.

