### Trial oversight and monitoring

The study will be reviewed and monitored annually by the Ethics Committee of the Jinling Hospital and the Data and Safety Monitoring Board whose members are from each center to ensure the safety of the participants and the validity of the data.

Termination of the trial may occur for the following reasons (determined by the Ethics Committee of the Jinling Hospital during their annual meeting):
Major mistakes are found in the trial protocol, making it difficult to evaluate the efficacy of the method.The trial has a major deviation in implementation and thus is difficult to continue.The sponsor requests to terminate the trial because of a lack of funding or poor management.

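### The annual stopping rule ends the trial when non-inferiority is not yet shown, although its own wording speaks of significant excess hazard; with true HR 1.0 it would stop about 80-88% of trials at the first review

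*Protocol article*

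**What the plan says.** The rule is in the last paragraph of the Statistical analysis section. The timing and the quantity compared across arms are given as "At the annual monitoring meeting of the Data and Safety Monitoring Board, the treatment effectiveness (the 12-month survival rate) will be compared between the two". The condition in words is "If one group has significantly more hazards than the other one". The only numerical criterion follows in parentheses, with its consequence: "upper limit of the 95% CI of the hazards ratio is more than 1.3), the trial will be terminated". No minimum number of deaths and no separate interim confidence level is given.

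Earlier in the same section the final success criterion reads: "If the upper limit of the 95% CI is less than 1.3, the non-inferiority is accepted". The Sample size section fixes the margin ("the non-inferiority limit of the hazards ratio (HR) is set to 1.3") and the planning assumption ("we assume a 1-year overall survival rate of 70% (mortality rate of 30%) in both the reference group and the new surgical group"), so the trial is planned on a true HR of 1.0.

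**The concern.** The words and the number describe different events. Significantly more hazard in one group requires the **lower** confidence limit of the HR to exceed 1. An **upper** limit above 1.3 is in effect the complement of the final success criterion, so it says that the data do not yet establish non-inferiority. That is the normal state of any non-inferiority trial at an early look.

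The sentence makes termination mandatory. A board that follows the number would very probably close a trial that is running exactly as planned, leave its question unanswered and record the reason as excess hazard. A board that follows the words has to set aside the only operational criterion in the article.

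**Working it through.** The article prints no operating characteristics for this rule, so there is no stated figure to reproduce. The 956 patients enter below only as the number to be enrolled; how that number was derived is a separate matter.

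**Inputs from the article**
- 956 patients, 1:1, 30% mortality at 12 months in both arms, margin HR 1.3 (Study design; Sample size).
- Annual looks and a 95% CI (Statistical analysis).
- Four years in total including 12 months of follow-up, hence about 3 years of recruitment. A start in January 2020 would give up to about 3.75 years (Trial status).

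**Assumptions of this check**
- Uniform accrual, and a first look one year after recruitment starts.
- The HR taken as endoscopic versus EVD only, unless stated otherwise.

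**1. Deaths needed for the limit to reach 1.3.** With 1:1 allocation and D deaths, SE(log HR) is about 2/√D. At an observed HR of 1.0 the upper limit is exp(1.96 × 2/√D). Setting this to 1.3 gives D = (3.92/0.2624)² ≈ 223. The whole trial expects 956 × 0.30 ≈ 287 deaths, so 223 is about 78% of them. At 40 deaths the limit at an observed HR of 1.0 is exp(3.92/√40) = 1.86, and the trial continues only if the observed HR is at most 1.3/1.86 = 0.70.

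**2. Deaths at the first look.** Under a constant hazard, λ = −ln 0.70 = 0.3567. For patients entering uniformly over the year, the expected proportion dead is 1 − 0.30/0.3567 = 0.159.
- 3-year accrual: 956/3 ≈ 319 enrolled, 50.6 deaths.
- 3.75-year accrual: 956/3.75 ≈ 255 enrolled, 40.5 deaths.

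**3. Probability of stopping at a true HR of 1.0.** P = 1 − Φ(ln 1.3 × √D/2 − 1.96).
- D = 50.6: 1 − Φ(0.933 − 1.96) = 84.8%.
- D = 40.5: 1 − Φ(0.835 − 1.96) = 87.0%.
- All 30% of deaths counted immediately (about 73 to 96 deaths, the lower end allowing 5% dropout): 80% to 75%.
- Slow accrual (100 to 200 enrolled, about 16 to 32 deaths): about 93% to 89%.

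**4. Simulated Cox fits.** 956 patients, follow-up capped at 12 months, 2,000 trials per cell. The early-weighted hazard is Weibull with shape 0.4 and the same 30% at 12 months. Each range runs over 3 and 3.75 years of accrual.

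| True HR | Stop at look 1, constant hazard | Stop at look 1, early-weighted | Stopped by look 2, all cells |
|---|---|---|---|
| 1.0 | 85-88% | 79-83% | 84-92% |
| 0.8 | 65-69% | 50-60% | 52-72% |
| 0.65 | 37-50% | 25-34% | 25-50% |

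**5. Both directions.** If the worse group is always the numerator, the observed HR is at least 1, so the upper limit is at least exp(3.92/√D). That exceeds 1.3 whenever D is below about 223, and the stop is then certain. In simulation every trial stopped at looks 1 and 2.

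**6. The words taken literally.** A lower 95% limit above 1 in either direction occurs in about 5% of trials per look at a true HR of 1.0.

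**The case against.** The strongest reply is that the lead-in shows the intent, and that the parenthesis is a drafting slip naming the wrong limit. That is plausible, and nobody can say that a board would in fact close an evenly balanced trial. But the parenthesis is the only criterion a board could apply, and the consequence is not discretionary. The reply explains how the contradiction may have arisen; it does not remove it.

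A second reply is that the percentages depend on accrual, timing of deaths, date of the first look and direction. This stands, and it is why ranges are given. The section also names the 12-month survival rate as the quantity compared. If only patients with completed follow-up counted, the first meeting would have almost no data and the problem would move to a later one.

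Two stronger readings are tempting and are not supported:
- A reader might infer that the trial stops in most cases even if endoscopy is clearly better. At a true HR of 0.65 the one-directional rule stops about half of trials or fewer by the second look.
- A reader might infer that the Trial oversight and monitoring section contradicts the rule, because its list ("Termination of the trial may occur for the following reasons (determined by the Ethics Committee") omits it. That list says what may lead to termination and does not claim to be complete, so the omission is not a contradiction.

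**Conclusion.** The rule is wrong as written: its numerical definition contradicts its own words and would stop the trial for lack of data. Under the planned true HR of 1.0 and the one-directional reading, termination at the first annual review has a probability of about 80-88% for uniform accrual over 3 to 3.75 years, and about 75-93% over wider assumptions on accrual and timing of deaths. At a true HR of 0.8 it is about 50-70%, and at 0.65 about 25-50%. On the two-directional reading, which the wording about one group and the other suggests, it is certain below about 223 deaths. No single percentage should be quoted without its direction and assumptions. The conclusion does not depend on the exact value, because no accrual pattern or hazard shape examined makes the rule workable at a true HR of 1.0.

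**What to change.** Remove the trigger based on an upper limit above 1.3, and make the criterion match the words: the board considers stopping for harm when the lower limit of the HR exceeds 1.0 at a stringent interim level stated in advance. State which arm is the numerator and whether the rule applies in both directions.

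Haybittle-Peto (99.9% CI, |z| > 3.29) is one example, not the only choice. Its price is low sensitivity at the first looks: at a true HR of 1.6, the simulations stopped only about 3-13% of trials at look 1 and 29-50% by look 2. A less extreme boundary would detect harm sooner at the cost of more false stops.

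If a stop for endoscopic superiority is kept as well, say that its effect on the final type I error is negligible at that level. Crossing z = −3.29 has probability about 0.0005 per look at a true HR of 1.0, and less at a true HR of 1.3. It should not be said that no early success claim is possible, since such a stop would be one.

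A cross-reference in the Trial oversight and monitoring section is optional but would help. The cost is a one-sentence amendment and matching text for the monitoring board; sample size and final analysis do not change.

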### Trial oversight and monitoring

The study will be reviewed and monitored annually by the Ethics Committee of the Jinling Hospital and the Data and Safety Monitoring Board whose members are from each center to ensure the safety of the participants and the validity of the data.

Termination of the trial may occur for the following reasons (determined by the Ethics Committee of the Jinling Hospital during their annual meeting):
Major mistakes are found in the trial protocol, making it difficult to evaluate the efficacy of the method.The trial has a major deviation in implementation and thus is difficult to continue.The sponsor requests to terminate the trial because of a lack of funding or poor management.

## Discussion

This study is a randomized controlled trial designed for patients with moderate to severe IVH. It aims to compare a relatively new surgical procedure (endoscopic IVH evacuation surgery) with the standard treatment (EVD). As with all surgical clinical trials, timing of the trial is crucial. If the trial is conducted too early, the new technique may still undergo too many modifications to allow application of a standardized procedure. In addition, recruitment might be too slow and the trial might turn out to be unfeasible. In contrast, if the trial is left too late, the new technique may become part of the mainstream treatment without adequate proof of its equivalence. In that case, too many patients might refuse randomization and the trial could also become unfeasible. Currently, the interest among endoscopy is strong and investigators are eager to enroll patients.

In summary, the available evidence suggests that endoscopic IVH evacuation surgery may be a valid alternative surgery to EVD with equal OS for patients diagnosed with moderate to severe IVH. This trial is aimed to provide high-quality evidence to support this hypothesis.

## Trial status

The trial was reregistered on July 25, 2019, at ClinicalTrials.gov and recruitment will begin in 2020. The programmed completion date for the recruitment is September 31, 2023, and will include a follow-up period of 12 months which means 4 years are needed to finish the trial. The trial is now in the recruitment stage. The protocol version number is V2.0 (April 23, 2019).

## Data Availability

The data are currently unavailable.

## Abbreviations

IVH: Intraventricular hemorrhage
ICH: Intracranial hemorrhage
EVD: External ventricular drainage
STICH: Surgical Trial in Intracerebral Haemorrhage
AHA/ASA: American Heart Association/American Stroke Association
rtPA: Recombinant tissue-type plasminogen activator
CLEAR: Clot Lysis: Evaluating Accelerated Resolution of Intraventricular Hemorrhage
CTA/MRA/MRV/DSA: Computed tomography angiography/magnetic resonance angiography/magnetic resonance venogram/digital subtraction angiography
SPIRIT: The Standard Protocol Items: Recommendations for Interventional Trials
RAT: Randomization Allocation Tool
CT: Computed tomography
OS: Overall survival
CI: Confidence interval
